#### Secondary outcome assessment

Analysis on the presence of CPTP will also be performed at 3 months and 12 months, whilst all remaining secondary outcomes will be analysed at each time point, as appropriate. The presence of CPTP and mortality will be analysed similarly to the primary outcome. Questionnaire responses (VAS, BPI, EQ-5D, HADS and SF-MPQ-2) will be converted to scores and analysed using a mixed linear regression model, adjusting for the intervention group, baseline score (if available) and the minimisation variables (again, centre will be included as a random effects variable). Further supportive analyses will be carried out on questionnaire responses using a repeated measures [31] (multi-level) model incorporating all recorded scores (baseline and the three post-treatment scores). Parameters allowing for participant, intervention group, time, baseline score and the minimisation variables will be included. A random intercept component will also be included. Regarding safety, the total number of patients experiencing SAEs will be reported by intervention group along with a descriptive table of the events, and statistical significance will be determined by a chi-square test.

A separate statistical analysis plan has been produced and provides a more comprehensive description of the planned statistical analyses.

### Interim analyses {21b}

Interim analyses of safety and efficacy for presentation to, and review by, the independent DMEC will take place during the trial. The committee will meet prior to trial commencement to agree on the manner and timing of such analyses, but this is likely to include the analysis of the primary and major secondary outcomes and full assessment of safety (SAEs) at least at annual intervals. Criteria for stopping or modifying the trial based on this information will be ratified by the DMEC. These interim analyses will be prepared by the Trial Statistician and shared solely with the DMEC. The chief investigator, trial management group and site investigators will be blinded to these interim analyses.

### Methods for additional analyses (e.g. subgroup analyses) {20b}

#### Subgroup analyses

Subgroup analyses will be limited to the same variables used in the minimisation algorithm (see Sect. 16a), apart from the centre. Tests for statistical heterogeneity (e.g. by including the treatment group by subgroup interaction parameter in the statistical model) will be performed before examining effect estimates within subgroups. The results of subgroup analyses will be treated with caution and will be used for hypothesis generation only.

#### QRI analyses

Full or targeted sections of interviews and audio-recorded appointments will be transcribed verbatim by an approved transcription service and edited to ensure the anonymity of the respondent. Data will be managed using NVivo software (NVivo v12., QSR International, Daresbuty, UK). Interview data will be analysed thematically using constant comparative approaches derived from Grounded Theory methodology [32]. Audio-recorded recruitment consultations and follow-up discussions will be interpreted using thematic analysis and other QuinteT methods [33].

#### Economic analyses

In order to assess the costs and benefits of PVB compared with TEB, both a within-study and a model based economic analysis will be undertaken.

Within study analysis—This component will use the data collected within the trial; estimates of cost-effectiveness will include the primary outcome within the trial; CPTP at 6 months post-randomisation. The principal economic analysis will assess cost-effectiveness based on incremental cost per quality adjusted life year (QALY) gained at 6 months post-randomisation, with a secondary analysis of cost per case of CPTP avoided at 6 months. If sufficient data is available, this analysis will be extended to cover outcomes and resource use at 12 months post-randomisation.

Model-based analysis beyond the end-point of the trial—If the trial shows that PVB is effective in reducing CPTP compared with TEB, it will be necessary to assess the cost-effectiveness of PVB in the longer term, in order to take into account the impact of chronic pain on an individual’s quality of life and productivity. Therefore, if deemed necessary based on the trial’s results, a decision-analytic model will be used to evaluate the longer-term impacts of the different types of analgesic. As a starting point, the model development process will use other models developed for chronic pain [34, 35]. The evidence used in the model will be drawn from the trial, with data on longer term costs and outcomes derived from the literature. If data availability permits, a societal perspective will be adopted alongside a healthcare perspective.

### Methods in analysis to handle protocol non-adherence and any statistical methods to handle missing data {20c}

Every effort will be made to collect full follow-up data on all trial participants; it is thus anticipated that missing data will be minimal. Participants with missing primary outcome data will not be included in the primary analysis in the first instance. This presents a risk of bias, and sensitivity analyses will be undertaken to assess the possible impact of the risk. This will consist of simulating the missing responses using a multiple imputation approach. Parameters used to simulate the missing responses will include the minimisation variables, intervention group, the participant’s previous responses at each time point and whether the value is missing due to death or other reason. It is not anticipated that the randomised interventions will be associated with the number of deaths, i.e. missing due to death is expected to be a random event. Additional sensitivity analysis on the primary outcome will involve varying the VAS thresholds to define CPTP as VAS worst chest pain (i) greater than 30 and (ii) greater or equal to 70.

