### Sample size {14}

Assuming a 30% incidence of CPTP in the TEB group (similar to that seen in our previous TOPIC-pilot trial results [12] and systematic review [13], 392 patients in each group will give 90% power (two-sided, *p* = 0.05) to detect a 10% absolute reduction (i.e. down to 20%, a 33% relative reduction) in the PVB group. Assuming a 10% rate of death by 6-month follow-up (similar to that seen in the TOPIC pilot) and a further 15% loss to follow-up at 6 months, we will recruit a total of 1026 participants.

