## Assignment of interventions: allocation

### Sequence generation {16a}

Participants will be randomised in a 1:1 ratio to either TEB or PVB. A minimisation algorithm will be used within the online randomisation system to ensure balance in the treatment allocation over the following variables:GenderAge < 65 years or ≥ 65 yearsCentreThoracotomy for lung cancer resection or for other indication

A ‘random element’ will be included in the minimisation algorithm, so that each participant has a probability (1:5), of being randomised to the opposite treatment that they would have otherwise received.

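### The missing-data sensitivity analysis, as worded, imputes 6-month pain scores for patients who have died, using a death predictor whose effect cannot be estimated

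*Protocol article*

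**What the plan says.** The relevant text is in the protocol article, section {20c} on non-adherence and missing data. Participants without a 6-month score are left out of the primary analysis. The section accepts that this could bias the result and names multiple imputation of the missing responses as the check. The imputation predictors are the minimisation variables, the arm, the participant's earlier responses, and "whether the value is missing due to death or other reason". No exception is made for patients who have died. The section then says that the interventions are not expected to affect the number of deaths, and restates this as "missing due to death is expected to be a random event".

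The Sample size section ({14}) treats death as a separate and sizeable source of attrition: "Assuming a 10% rate of death by 6-month follow-up", followed by a further 15% lost to follow-up. The primary outcome (Outcomes {12}) is the participant's own rating of worst chest pain over the previous week, dichotomised at 40 mm. The article does not say what that rating means for someone who has died.

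**The concern.** Three things look wrong in one short paragraph.

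- **Target.** The primary analysis rests on survivors who returned the questionnaire. Extending it to survivors who did not respond is the normal purpose of imputation. Extending it to the dead is different: their 6-month pain is not unobserved, it does not exist. The two analyses then describe different populations.
- **Predictor.** A reason for missingness has meaning only where the score is missing. A model for the 6-month score learns from patients whose score is present, and none of them is missing because of death.
- **Justification.** Equal numbers of deaths by arm concern the relation of death to treatment. They say nothing about the relation of death to pain. The Background notes that thoracotomy is most often done for lung cancer, so patients who die within 6 months may well differ in pain from those who live.

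At stake is how clearly the one analysis named against bias from missing outcomes can be read. The section hopes for little missing data, but the sample size allows for nearly a quarter.

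**Working it through.** **1. Reproduce the plan's figures.** Inputs from Sample size {14}: "Assuming a 30% incidence of CPTP in the TEB group", 20% in the PVB arm, "two-sided, *p* = 0.05", and "392 patients in each group will give 90% power". Allocation is 1:1 (Sequence generation {16a}).

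n per arm = [1.960 × √(2 × 0.25 × 0.75) + 1.282 × √(0.3 × 0.7 + 0.2 × 0.8)]² / 0.10² = 392 after rounding up. Power at 392 per arm is 0.900.

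Inflation: 784 / (0.90 × 0.85) = 1024.8, or 392 / 0.765 = 512.4, rounded up to 513 per arm and 1026 in total. So the 15% applies to survivors. Adding the two losses gives 784 / 0.75 = 1045.3, which does not fit.

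**2. How many imputed values belong to the dead.**

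- Deaths: 1026 × 0.10 = 102.6
- Other losses: (1026 − 102.6) × 0.15 = 138.5
- Total missing: 241.1, which is 23.5% of 1026
- Observed: 1026 − 241.1 = 784.9
- Share of imputed values belonging to the dead: 102.6 / 241.1 = 42.6%

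**3. Can the death predictor be estimated?** Among patients with an observed 6-month score, the indicator for missing because of death is 0 for everyone. A column of zeros adds nothing to the rank of the design matrix. A check used 1026 simulated patients with 10% deaths and 15% further loss, of whom 784 had an observed score. The columns were intercept, arm, sex, age group, indication, 3-month score and death indicator. The matrix had rank 7 over all patients but rank 6 of 7 among the observed, and its cross-product was singular. Coding the reason in three levels gave 8 columns and again rank 6. The coefficient is not identified under either coding.

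**4. What imputing the dead does to the result.** Take survivor risks of 30% (TEB) and 20% (PVB), with 10% dead in each arm. With imputed risks qT and qP for the dead:

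RR = (0.9 × 0.20 + 0.1 × qP) / (0.9 × 0.30 + 0.1 × qT)

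- Dead drawn from the survivors' model (qT = 0.30, qP = 0.20): 0.20 / 0.30 = 0.667, risk difference 10 points, no change.
- Same risk in both arms, 10%: 0.19 / 0.28 = 0.679, difference 9 points.
- Same risk in both arms, 30%: 0.21 / 0.30 = 0.700, difference 9 points.
- Same risk in both arms, 50%: 0.23 / 0.32 = 0.719, difference 9 points.

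The first line is what the written plan delivers once the predictor drops out, because arm and earlier scores remain in the model. It is exact only if the dead resemble the survivors in those earlier scores. The other lines need an assumption that the article does not make.

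**The case against.** The best defence is that one redundant term in one sensitivity analysis does little harm. The model runs once the term is dropped. The dead are then given the survivors' arm effect, so the relative risk hardly moves. A reason-for-missingness variable can also serve as a marker for an analyst-set offset (a delta or pattern-mixture approach), and the separate statistical analysis plan may describe one. Finally, all-cause mortality is a secondary outcome analysed by arm, so an imbalance in deaths would be seen.

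Much of this stands, and it limits the point. Several stronger readings are tempting, and the document does not support them:

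- A reader might infer that the imputation cannot be run at all. It cannot be run with that predictor acting as an estimated effect; the rest of the model is unaffected.
- A reader might infer that imputing the dead by itself moves a relative risk of 0.67 towards 0.70 or beyond. That requires giving the dead equal risk in both arms, which the plan does not do.
- A reader might infer that comparing the two analyses tells us nothing. About 139 of the 241 imputed values (57%) belong to surviving non-responders, so the check is diluted but not void.

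The rest of the defence does not cure the text. The article states this predictor and describes no offset. The flag might be estimable in an equation for an earlier score, such as month 3, but not in the one for the 6-month outcome. Reporting deaths by arm tests whether death relates to treatment, not whether it relates to pain.

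**Conclusion.** The point holds as an error in a stated rule, with limited consequences. As worded, the analysis creates 6-month pain scores for about 103 patients expected to have died, 43% of all imputed values. It relies on a predictor that cannot contribute to the model for that outcome, so the deaths would be handled as if they were lost questionnaires, although the wording sets them apart. The inference from no association with arm to a random event is not valid where pain is concerned.

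The count rests on the plan's assumed 10% deaths and 15% further loss among survivors. The effect on the relative risk is probably small, and about nil if the dead are drawn from the survivors' model and resemble survivors in their earlier scores. It would reach a few hundredths only under an added assumption about their risk. The primary analysis, its p-value and the sample size do not depend on this. It should be fixed, but it does not threaten the main result.

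**What to change.** In section {20c}, and in the analysis plan if it repeats the wording:

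1. State that the sensitivity analysis addresses CPTP among patients alive at 6 months after randomisation.
2. Restrict multiple imputation to those survivors whose 6-month VAS is missing, keeping the minimisation variables, arm and other recorded scores as predictors. On the plan's rates this means about 139 imputed values in about 923 patients.
3. Delete the predictor for death or other reason.
4. Remove the inference that death is a random event. The expectation that deaths will not differ by arm can stay as an expectation.

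No further step is needed to report deaths by arm, since mortality is already a secondary outcome. A composite of death or CPTP in all patients would be an optional supportive analysis, not a correction.

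The cost is a few lines of text. No new data are needed, because the participant timeline already has a mortality check at month 6. The downside is that the result is explicitly conditional on survival, as the complete-case primary analysis already is. The change is best made before anyone has seen outcomes by arm.

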### Plans to give access to the full protocol, participant level-data and statistical code {31c}

The full protocol is publicly assessable online via the trial website [36]. The datasets generated during the current study can be made available by the chief investigator upon reasonable request and in agreement with the research collaboration and data transfer guidelines of Birmingham Clinical Trials Unit.

## Oversight and monitoring

### Composition of the coordinating centre and trial steering committee {5d}

#### Trial management group

The trial management group will be chaired by the chief investigator and include clinical trials unit, clinician, statistical, health economic, qualitative and patient and public partner representation. This group will monitor all aspects of the conduct and progress of the trial, ensure that the protocol is adhered to and take appropriate action to safeguard participants and the quality of the trial itself. This group will meet approximately monthly though it will meet more frequently as required by ongoing trial activities.

#### Trial steering committee

A single trial steering committee (TSC) will be created for the TOPIC 2 trial and meet face-to-face or via teleconference at least once prior to recruitment of the first patient, then at least annually until full publication of TOPIC 2, and as required depending on the needs of the trial office. The TSC will be led by an independent chair and, as per NIHR HTA guidelines, will be composed of an independent statistician, health economist, clinician, patient representative and observers. Membership and duties/responsibilities are outlined in the TSC charter. In summary, the TSC will provide overall oversight of the trial, including the practical aspects of the trial, as well as ensuring that the trial is run in a way which is both safe for the patients and provides appropriate data to the sponsor and investigators.

### Composition of the data monitoring committee, its role and reporting structure {21a}

A data monitoring and ethics committee (DMEC) will be led by an independent chair who is an expert in the field. As per NIHR HTA guidelines, the DMEC will be composed of an independent expert statistician and clinician. Data analyses will be supplied in confidence, and the DMEC will be asked to advise whether the accumulated data from the trial, together with the results from other relevant research, justify the continuing recruitment of further participants. The DMEC will operate in accordance with a trial specific charter based upon the template created by the Damocles Group [37]. The DMEC will meet at least annually as agreed by the committee and documented in the charter.

### Adverse event reporting and harms {22}

The safety profile for the trial population and trial interventions are well established; therefore, a strategy of targeted recording of AEs is being employed which it is believed will not affect the safety of participants. Defined, expected complications of regional anaesthesia and postoperative surgical complications (Table 4) will be collected in trial specific CRFs.

**Table 4 Tab4:** Protocol defined anticipated complications of regional analgesia and surgery

Category	Complication
Complications of regional/systemic analgesia	Nausea Vomiting Post-dural puncture headache Block failure Vascular puncture Pleural puncture Hypotension Urinary retention Drowsiness Itching High Block Inadequate pain relief
Surgical complications	Bronchopleural fistula Prolonged air leak Pneumothorax Surgical emphysema Post-surgical bleed Chylothorax
Respiratory complications	Atelectasis Pneumonia ARDS Pulmonary aspiration Pulmonary embolism Pleural effusion
Cardiovascular complications	Atrial arrythmia Ventricular arrythmia Myocardial infarction Deep venous thrombosis
Renal complications	Renal failure
Neurological complications	Transient or permanent neurologic deficit Coma

Beyond these defined, expected complications, adverse events will be reported in accordance with the UK Policy Framework for Health and Social Care Research, the Principles of GCP as set out in the UK Statutory Instrument (2004/1031; and subsequent amendments) and the requirements of the Health Research Authority (HRA). When completing an SAE form, the principal investigator or medically qualified delegate will be asked to define the causality and the severity of the SAE. On receipt of an SAE form at the trial office, the chief investigator or delegate will independently determine causality of the SAE. An SAE judged by the PI, CI or delegate(s) to have a reasonable causal relationship with the intervention will be regarded as a related SAE. The CI or delegate(s) will assess all related SAEs for expectedness. If the event is unexpected, i.e. is not defined in the protocol as an expected event, it will be classified as an unexpected and related SAE.

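### Relatedness of an SAE is judged against the block, but expectedness against a list that also covers surgery, so a coma or permanent neurologic deficit attributed to the block would be labelled expected

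*Protocol article*

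**What the plan says.** All of this is in the protocol article, Adverse event reporting and harms {22}, unless stated otherwise.

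- **Related.** An SAE that the site or the chief investigator (or a delegate of either) judges to have a "reasonable causal relationship with the intervention will be regarded as a related SAE". Under Trial design {8} and Intervention description {11a}, the intervention is TEB or PVB, not the thoracotomy.
- **Assessed for expectedness.** "The CI or delegate(s) will assess all related SAEs for expectedness".
- **Unexpected.** If the event "is not defined in the protocol as an expected event, it will be classified as an unexpected and related SAE".
- **The list.** "Defined, expected complications of regional anaesthesia and postoperative surgical complications (Table 4) will be collected in trial specific CRFs". Table 4 is titled "Protocol defined anticipated complications of regional analgesia and surgery". It has six rows: "Complications of regional/systemic analgesia", surgical, respiratory, cardiovascular, renal and neurological. The neurological row reads "Transient or permanent neurologic deficit Coma", which is two entries run together.
- **A second list.** Outcomes {12} and footnote F of Table 2 set out complications of regional analgesia on their own. Both include a low respiratory rate (below 10/min). Neither includes coma, neurologic deficit, myocardial infarction or renal failure.

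**The concern.** The two halves of the classification refer to different things. Causality is judged against the block, while expectedness is judged against a list for the block and the operation together. A grave event can be anticipated after a thoracotomy without being an anticipated consequence of a nerve block. Once assessors have decided that the block caused it, the useful question is whether it is anticipated for the block. The rule as written does not ask that.

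At stake is a case-level safety label. Unexpected and related is the only special category of event that this section defines, and it would be withheld from some of the most serious events on the list when they are attributed to a randomised technique. Such events are likely to be too few for a between-arm count of SAEs to show much, so the classification of each single case carries weight.

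**Working it through.** The plan gives no figure for this point. The check is a count of the list and a walk through the rule.

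**Count of Table 4**

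| Row | Entries |
|---|---|
| Regional/systemic analgesia | 12 |
| Surgical | 6 |
| Respiratory | 6 |
| Cardiovascular | 4 |
| Renal | 1 |
| Neurological | 2 |
| Total | 12 + 6 + 6 + 4 + 1 + 2 = 31 |

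Entries outside the analgesia row: 31 − 12 = 19, and 19/31 = 61%.

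**Analgesia row against the separate outcome list.** The list in Outcomes {12} has 12 items, with nausea and vomiting counted as one. Table 4 counts them as two, so its 12 entries correspond to 11 items of the outcome list. The one item left over is low respiratory rate, which appears in no row of Table 4.

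**The rule applied to two serious events, each attributed to the block**

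| Step | Coma or permanent neurologic deficit | Low respiratory rate |
|---|---|---|
| Attributed to the block, so related? | Yes | Yes |
| Named in the separate list of regional-analgesia complications (Outcomes {12}; Table 2, footnote F)? | No | Yes |
| Named in Table 4? | Yes, neurological row | No |
| Label under the rule | Expected | Unexpected and related |

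For both events the label is the reverse of what the protocol's own list of block complications would give. Myocardial infarction (cardiovascular row) and renal failure (renal row) follow the same path as coma. At no step does the rule look at the table row, the attributed cause or the severity.

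**What still happens to such an event.** Causality is decided by the site and, independently, by the chief investigator or a delegate, and does not depend on expectedness. Secondary outcome assessment, under {20a}, reports patients with SAEs by arm, with a descriptive table and a chi-square test. Interim analyses {21b} says that the reports to the DMEC are likely to include a full SAE assessment at least once a year. Under {23}, routine on-site monitoring covers only the first five recruiting sites, but unusual SAE reporting rates can trigger further visits.

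**The case against.** A reader might infer more than the documents support, in three ways.

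1. **That a block-attributed coma can never be classed as unexpected and related.** This holds only for the article's text. The rule refers to events defined in the protocol, and the full protocol (V5.0) is not shown. It could define expectedness separately for the intervention. This limit stands. It does not remove the point, because the article does not merely leave the definition out: it states an operative rule, and that rule gives the wrong label when applied to the list beside it.

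2. **That the 19 other entries are on the list because the operation causes them.** No sentence says so. The title of Table 4 covers both causes, and its last four rows are named by organ system, not by cause. The sponsor may have meant some of these events to be anticipated for the block as well. The 61% therefore counts entries outside the analgesia row and is not a count of errors. Against the deliberate reading, the protocol's separate list of regional-analgesia complications leaves out coma, neurologic deficit, myocardial infarction and renal failure, and Table 4 leaves out low respiratory rate. That pattern does not look like a considered list for the block.

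3. **That the safety alarm is switched off, so that a cluster in one arm would go unseen.** The documents contradict this. Comparing arms is the work of the SAE tabulation and the DMEC review, and neither depends on expectedness. The event is still captured and can still be called related.

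A fair objection also applies to the simplest remedy, which is to test expectedness against the analgesia row alone. That row omits low respiratory rate. A pneumothorax attributed to a pleural puncture would become unexpected, although the row lists pleural puncture itself. The fix below allows for this.

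**Conclusion.** The point holds for the rule as the article states it. Relatedness is tied to the block, expectedness is tied to a combined list, and the result is a wrong label in both directions: grave events outside the protocol's own list of block complications come out as expected, and one event on that list comes out as unexpected.

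The loss is the unexpected-and-related classification, not the data. The number of patients affected cannot be derived from the documents and is probably small. The primary outcome and its analysis are untouched. The correction is still worth making, because the events concerned are among the most serious on the list and the change is cheap.

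The conclusion rests on two assumptions: that Table 4 is the list meant by the expectedness rule, since no other is shown, and that the full protocol does not define expectedness separately for the block. The statement that nothing is lost also assumes that a serious event named in Table 4 still goes onto an SAE form. The article describes general adverse event reporting for events beyond the listed ones, so this is not entirely clear.

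**What to change.** In Adverse event reporting and harms {22}:

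- State that the expectedness of an intervention-related SAE is judged only against events listed as anticipated complications of the block.
- Build that list from the analgesia row of Table 4, reconciled with Outcomes {12} and footnote F of Table 2. The known difference is low respiratory rate.
- Have the sponsor mark explicitly any other Table 4 event that it regards as anticipated for the block. Which events those are is for the sponsor and investigators to decide.
- Keep the remaining rows of Table 4 for CRF recording of surgical complications.

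The cost is a sentence in the protocol, a marked-up table, a line on the SAE form and a few more unexpected-and-related reports. If V5.0 already defines expectedness for the intervention, it is enough to bring the article's wording into line with it.
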